##### Organizational readiness

The implementation of the educational strategies to increase the use of NIV in COPD exacerbations will require the coordinated action of many organizational members (e.g., physicians, RTs, and nurses). The organizational readiness for implementing change (ORIC) survey can assess this construct at the supra-individual level (team, department, or organization) [34]. When organizational readiness is low, clinicians at these hospitals are likely to see the implementation (educational strategies) for the intervention (NIV use in COPD exacerbations) as undesirable and potentially avoid or resist planning for the implementation or participating in the implementation [34, 35]. The ORIC will allow us to identify the difference between organizations resisting the change (increasing NIV utilization) and sites that are unable to implement the educational strategies due to difficulties inherent in organizing and conducting the educational strategies at their hospital. To assess the readiness of the organization to implement the change, we will use a 7-item survey adapted from the original 10-item organizational readiness for implementing change (ORIC) [34]. This survey will measure change commitment and change efficacy of the organization towards increasing the rate of NIV use for COPD exacerbations.

##### Power and sample size for aim 1

The minimal number of hospitals participating in the trial was based on the analysis of Premier 2016–2017 data. Hospital RS-NIV proportions were calculated for the 457 hospitals with at least 35 eligible COPD admissions. The median RS-NIV rate among this group of hospitals was 82% (IQR 74–86%). We then selected the 48 hospitals with RS-NIV proportion less than 55%, based on the clinical impression that these hospitals would have sufficient room for improvement, as potentially eligible sites. Among these hospitals, the median number of eligible COPD patients was 197 over a 12-month period, ranging from 23 to 556 patients. The number of ventilated patients per hospital ranged from 7 to 163, with a median of 37. To achieve stability in estimation of hospital level RS-NIV, we will assess our primary endpoint at 18 months post-intervention expecting a minimum of 10 ventilated patients per hospital in which to assess NIV rates. Power analysis was conducted to determine the number of hospitals needed to assess the primary outcome of difference between the study arms in change in the hospital level risk-standardized proportion of ventilator starts that are NIV (RS-NIV). Using a type I error rate of 0.05, and standard deviation of change in rates over time derived from our prior work with the Premier data base, a total sample of 20 hospitals, 10 in each arm will give 80% power to detect difference of 15% in change (e.g., 5% increase among OLE hospitals, vs. 20% increase among IPE hospitals). Power is > 90% to detect a 20% difference in change between the intervention groups.

#### Aim 2

To examine the effect of OLE and IPE on RT autonomy and team functionality as potential mediators of NIV uptake.

##### Study design

To complete this aim, we will survey clinicians at baseline, 1 year, and end of the study period.

##### Participants and settings

We will select a random sample of 10 RTs for the RT survey and 21 providers (7 from each discipline) for team functionality and organizational readiness for change surveys. A waiver of consent will be sent to all potential participants via email, the survey link will be included at the end of the email. To maximize participation, we will provide $25 incentives to participants.

##### RT autonomy

Job autonomy is defined as the degree of perceived control that an employee has over how they perform tasks and the degree to which they operate independently. Prior studies showed that it mediates the relationship between employment status, work attitude, and performance [36, 37]. In our previous study, in-depth interviews with key stakeholders from a sample of hospitals with high use of NIV suggested that RT autonomy is critical to achieving timely initiation of NIV, often facilitated by the use of protocols [15]. These results are in line with prior literature [38] that supports the benefits of autonomous RT practice for weaning from IMV [39, 40]. Factors identified by the interviewees to contribute to RT autonomy were RT-driven protocols, RT expertise, and collegial relationship between RT and physicians. We assume that IPE will increase the physicians trust in RTs by allowing them to learn about their abilities and duties and concerns, and that IPE will facilitate team member recognition of their own knowledge with RTs being more likely to “speak up” (e.g., to suggest NIV use instead of intubation). To assess RT autonomy, we adapted a survey from the 11-item job autonomy measure from Aarons et al [37].

##### Team functionality

The IOM 2001 and 2006 quality chasm reports brought widespread attention to clinical teamwork as a means of improving safety and quality in healthcare [41]. Engagement in training-related activities designed to disseminate knowledge, skills, and attitudes for teamwork (such as IPE) is one way to acquire attitudes and behaviors consistent with teamwork and improve downstream impact on care quality and safety for patients [42–44]. get all clinicians (physicians, RTs, and nurses) involved in the delivery of NIV with the goal of promoting mutual trust and effective communication which will improve team functionality and hopefully promote NIV use. To assess team functionality, we adapted questions from the 4-point Likert scale Assessment of Collaborative Environment survey (ACE-15), a 15-item questionnaire which measures the perception of interprofessional “teamness” [45]. We created an 18-item questionnaire that has been divided into two parts: the first is the 9-item measure team functionality in managing patients with COPD exacerbation and the second is the 9–item measure team functionality in initiating NIV.

##### Statistical analysis

We will develop a series of models evaluating associations among the intervention, mediators, and outcome, including a structural equation model (SEM) to estimate the role of mediators as well as the direct effect of intervention on the outcome [46–49]. First, to evaluate the impact of educational intervention on the mediators RT autonomy and team functionality to implement change, multi-level models will be fit, clustering on hospital. Additional models will adjust for hospital and practitioner characteristics. Next, models for the primary RS-NIV outcome will be fit, with these potential mediators as the primary predictors. Main effects and interaction models will be evaluated. Then, the mediators will also be included as covariates in multi-level models including intervention, to evaluate whether RT autonomy and team functionality have effects on outcome, and after controlling for intervention. Finally, multi-level structural equation modeling will then be employed to estimate the indirect effect of the educational intervention on RS-NIV in the presence of mediators. Analysis will be performed using STATA’s gsem. This model will allow estimation of the direct effect of IPE intervention relative to OLE, in addition to the impact through the mediators (Fig. 5).

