**Fig. 5 Fig5:**
[figure not shown]
Mediation analysis. Key: RT = Respiratory Therapist, NIV = Noninvasive Ventilation

##### Power and sample size for aim 2

For aim 2 analyses, power was assessed for educational mode impact on job autonomy for respiratory RT measured by Aaron’s Job Autonomy Survey (AJAS), and team functionality measured by the ACE-15 tool. Estimating sample size to achieve 80% power, using a type I error rate of 0.05, a sample of 10 RT’s per hospital, will allow us to detect a moderate (Cohen’s *d* = .4) difference in AJAS at a 1-year post-intervention. This is accounting for clustering on hospital with intraclass correlation (ICC) in the range of .10–.20. Based upon data from local area hospitals, we estimate staffing of 8–10 RTs per 100 beds. For a few smaller hospitals, we will hope to include all RTs and may fall short of 10. Similarly, for the ACE-15, a sample size of 21 clinicians (7 each of RTs, RNs, and MDs) will achieve 80% power to detect a moderate effect size difference, accounting for clustering within hospitals, with ICC in the range of .10–.20 [50].

#### Specific aim 3

To evaluate the acceptability and feasibility of the IPE and OLE strategies and to inform further refinement of the strategies.

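### Aim 2 collects baseline autonomy and team-functionality scores, but no stated Aim 2 model uses them; this gives up precision and leaves the mediator-to-outcome path open to pre-existing hospital culture

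*Protocol article*

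**What the plan says.** All references are to the Protocol article.

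- **Aim 2, Study design:** "we will survey clinicians at baseline, 1 year, and end of the study period".
- **Aim 2, Statistical analysis:** for the effect of training on RT autonomy and team functionality, "multi-level models will be fit, clustering on hospital". Then: "Additional models will adjust for hospital and practitioner characteristics". Later steps use the mediators as predictors of the hospital's risk-standardised NIV proportion (RS-NIV) and fit a multi-level SEM for the indirect effect. The section names no survey wave and no baseline score.
- **Power and sample size for aim 2:** the only dated contrast is a "difference in AJAS at a 1-year post-intervention", sized at d = 0.4 "with intraclass correlation (ICC) in the range of .10–.20". No baseline-to-follow-up correlation is among the inputs.
- **Statistical analysis of aim 1:** baseline handling is stated twice, as change in RS-NIV from baseline and as a secondary comparison of post-intervention levels adjusted for baseline.
- **Randomization:** stratified by baseline NIV proportion and bed size, not by autonomy or team functionality.

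**The concern.** A baseline measure of each mediator is scheduled in both arms, yet the stated models make no use of it. Three things are at stake.

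1. **Precision.** With 20 hospitals, between-hospital variation dominates the error. A baseline hospital mean may explain part of it at almost no cost.
2. **Interpretation.** If the arms happen to differ in autonomy or teamwork before training, an unadjusted 1-year difference will be hard to read.
3. **Mediation.** Randomisation protects the arm-to-mediator comparison. It does not protect the mediator-to-outcome path, because hospitals are not randomised to levels of autonomy or teamwork. The RT autonomy section reports earlier interviews suggesting that autonomy is critical to starting NIV promptly. Prior culture could therefore drive both the 1-year score and RS-NIV, and an SEM without the baseline score may credit that to training.

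**Working it through.** **Inputs.** 10 hospitals per arm (Power and sample size for aim 1); 10 RTs per hospital for autonomy, 21 clinicians for team functionality; ICC .10–.20; d = 0.4 for autonomy; alpha 0.05 and 80% power (Power and sample size for aim 2). Assumed, because not stated: a two-sided test; d = 0.4 for the effect called moderate in team functionality; all correlations over time. Scores are in SD units.

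**1. The plan's own figure.** Design effect = 1 + (m − 1) × ICC.
- Autonomy, m = 10: 1.9 to 2.8; effective n per arm 100/1.9 = 52.6 to 100/2.8 = 35.7; SE = √(2/n) = 0.195 to 0.237; power = Φ(0.4/SE − 1.96) = 54% to 39%. The stated 80% appears only at ICC = 0 (80.7%).
- Team functionality, m = 21: 66% to 45%.

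The unadjusted 1-year contrast is therefore short of precision.

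**2. Chance imbalance in true arm means.** SD = √(2 × ICC/10) = 0.141 (ICC .10) and 0.200 (ICC .20).
- P(|difference| ≥ 0.2) = P(|Z| ≥ 1.41) = 16%, and P(|Z| ≥ 1.00) = 32%. Here 0.2 is half the target effect.
- If true hospital scores correlate r = 0.5–0.8 over the year, the part carried to 1 year has SD 0.5 × 0.141 = 0.07 to 0.8 × 0.200 = 0.16. It reaches 0.2 in about 0.5–21% of randomisations.

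**3. Effect on the test.** Hospital means were simulated 40,000 times with no effect of training, m = 10, fresh respondents at each wave and r = 0.8.

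| | ICC .10 | ICC .20 |
|---|---|---|
| Type I error, unadjusted | 5.1% | 5.0% |
| Type I error, baseline-adjusted | 5.0% | 5.0% |
| False finding for IPE when the baseline gap is in the top 10% favouring IPE, unadjusted | 8.5% | 12.5% |
| Same, baseline-adjusted (nominal 2.5%) | 2.2% | 2.2% |

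**4. Variance saved by adjusting for the hospital baseline mean, fresh respondents.** Variance of a hospital mean V = ICC + (1 − ICC)/m. Correlation of hospital means ρ = r × ICC/V. Variance is cut by ρ².

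| | V | ρ² at r = 0.5 | ρ² at r = 0.8 |
|---|---|---|---|
| Autonomy, ICC .10 | 0.190 | 7% | 18% |
| Autonomy, ICC .20 | 0.280 | 13% | 33% |
| Team, ICC .10 | 0.143 | 12% | 31% |
| Team, ICC .20 | 0.238 | 18% | 45% |

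Estimating the slope with 20 hospitals inflates variance by about 1/(20 − 4) = 6%. Net saving for autonomy: 1 − 0.931 × 1.0625 = 1% at the low end and 1 − 0.673 × 1.0625 = 28% at the high end. For team functionality: 1 − 0.8775 × 1.0625 = 7% to 1 − 0.548 × 1.0625 = 42%.

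**5. Power after adjustment** (d = 0.4; ICC .10, then .20; slope loss not deducted).

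| Scenario (assumed) | Autonomy | Team functionality |
|---|---|---|
| Fresh respondents, hospital correlation 0.8 | 62%, 54% | 82%, 70% |
| Same respondents, hospital 0.8, individual 0.5 | 78%, 68% | 92%, 79% |
| Same respondents, hospital 0.9, individual 0.7 | 93%, 88% | 99%, 96% |

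**The case against.** **The text does not exclude baseline.** A reader might infer that Aim 2 analyses only the 1-year level. The article does not say so: the analysis section names no wave, a third survey runs at study end, and the 1-year contrast appears only in a sample-size calculation. This stands, so the point is confined to what the stated models contain. It is also fair that an article condenses and that a full analysis plan may settle the matter. But this section does set out the model sequence, the classes of covariate, the SEM and the software, and Aim 1 in the same article states its baseline handling. Adding the baseline term is a specific improvement on the stated model.

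**Chance imbalance is not bias.** A reader might infer that baseline differences would pass for a training effect. With clustering modelled, they are part of the error the test already allows for, and type I error stays near 5%. This stands. The harm is conditional on an imbalance that is seen.

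**The size of the imbalance can be overstated.** The observed baseline difference has an SE of 0.195–0.237 for autonomy, which would put gaps of at least 0.2 at 30–40%. That includes sampling noise from the baseline respondents, which does not carry forward if fresh people answer later. The 16–32% for true means is the relevant figure.

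**The ICC does not show stability.** It describes clustering at one time and says nothing about persistence over a year. The correlations of 0.5–0.8 are assumptions, and at their low end the net gain for autonomy is close to nil. This stands too.

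**Conclusion.** The point holds as a recommended improvement, not as an error that invalidates Aim 2. Baseline mediator scores are collected and no stated Aim 2 model uses them. Three consequences remain:

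- a loss of precision, from almost nothing to substantial depending on a correlation the article does not give;
- a result that is easy to misread in the 16–32% of randomisations where true arm means differ by at least 0.2 SD;
- a mediator-to-outcome path that randomisation does not protect from prior hospital culture. This last consequence does not depend on any imbalance between arms.

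The 16–32% rests on the article's ICC range and 10 hospitals per arm. The variance savings rest on assumed correlations of 0.5–0.8.

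The stated 80% power does not reproduce from the unadjusted 1-year contrast. A reader might take this as a sign that baseline adjustment was intended. The article does not say so, and among the scenarios tried for autonomy only the strongest, with the same respondents and correlations of 0.9 and 0.7, exceeds 80% across the ICC range. That discrepancy is a separate matter and is not needed for this point.

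**What to change.** In Aim 2, Statistical analysis:

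- Compare the 1-year mediator score between arms in the multi-level model with the hospital's baseline mean on the same scale as a covariate.
- Include the same baseline term in the models with the mediators as predictors of RS-NIV and in the SEM. This reduces confounding by prior culture but does not remove every source of it.
- State whether the survey waves re-contact the same clinicians or draw fresh samples. Add the respondent's own baseline score only if the same clinicians are re-surveyed.

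The cost is one hospital-level degree of freedom per mediator model and a change of wording. The baseline survey is already scheduled, so no new data are needed for the hospital-mean term.

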**Methods and design:**

Twenty hospitals with low baseline rates of NIV use will be randomized to either the OLE or IPE study arm. The primary outcome of the trial is change in the hospital rate of NIV use among patients with COPD requiring ventilatory support. In aim 1, we will compare the uptake change over time of NIV use among patients with COPD in hospitals enrolled in the two arms. In aim 2, we will explore mediators’ role (respiratory therapist autonomy and team functionality) on the relationship between the implementation strategies and implementation effectiveness. Finally, in aim 3, through interviews with providers, we will assess acceptability and feasibility of the educational training.

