##### Primary outcome

Hospital-level risk-standardized (RS) initial NIV proportion among patients hospitalized with a COPD exacerbation that were ventilated with NIV or IMV is assessed via administrative records of patients discharged from participating premier hospital who were 40 years or older and received a principal diagnosis of COPD, or a principal diagnosis of acute respiratory failure paired with a secondary diagnosis of COPD. We will use a previously validated set of ICD-10-CM codes that achieve a reasonable balance of sensitivity and specificity while minimizing potential biases [30].

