We will generate descriptive statistics overall, by hospital and educational strategy, including counts and percentages for categorical data, means, standard deviations, and percentile distributions for continuous data. We will compare characteristics of hospitals, including staffing characteristics, in the two study arms via chi-square tests and *t* tests or Wilcoxon tests. Characteristics of patients in the enrolled hospitals in the two arms will be compared via GEE models accounting for clustering by hospital. We will calculate the percentage of patients treated according to each of the primary ventilatory strategies: no assisted ventilation, NIV, and IMV. We will then calculate the proportion of patients initially treated with NIV among those who received assisted ventilation. We will estimate a risk-standardized proportion of ventilated patients initially treated with NIV (RS-NIV) for each hospital and for each data collection period (baseline period, 18 months post-intervention, and between 18 to 36 months post-intervention). We will use hierarchical logistic regression with a random hospital effect to model initial use of NIV among patients started on ventilation, adjusting for demographics, and comorbidities. From the model, a predicted NIV percentage for each hospital will be computed as the NIV percentage that would be anticipated at a particular hospital by using its hospital random effect, given the patient case mix. The expected NIV percentage will be computed as the rate that would be expected if the same patient mix were treated at an “average” hospital, using the average hospital effect. The RS-NIV percentage is then computed as the ratio of predicted to expected NIV percentage standardized by the overall unadjusted mean NIV percentage for all admissions in our model. Risk standardization has 2 key advantages: it adjusts for differences in patient mix, which may impact the suitability of NIV; it also provides more stabilized estimates based upon Bayesian shrinkage towards the overall mean among hospitals with small numbers of ventilated patients [32, 33]. The mean and median RS-NIV rates of the two arms will be computed for each study period. The primary analysis will use an analysis of variance model to compare IPE to OLE on change in RS-NIV rates from baseline to 18 months post-intervention. Additional analyses will adjust for hospital characteristics that are unbalanced between the study arms. A secondary analysis will compare the post-intervention levels, adjusting for baseline RS-NIV. To assess sustainability, similar models will be used to compare level of RS-NIV after an additional 18 months have passed.

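### The Aim 2 mediation models do not say whether RS-NIV enters as level or change and name no baseline term, so the unrandomised mediator-to-outcome path can be biased in either direction

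*Protocol article*

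**What the plan says.** The Aim 2 section headed Statistical analysis sets out four steps.

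1. Multi-level models of the effect of arm on RT autonomy and team functionality. The only adjustment sentence of the section comes here: "Additional models will adjust for hospital and practitioner characteristics".
2. Then, "models for the primary RS-NIV outcome will be fit, with these potential mediators as the primary predictors".
3. Next, "the mediators will also be included as covariates in multi-level models including intervention".
4. Finally, "multi-level structural equation modeling will then be employed to estimate the indirect effect of the educational intervention on RS-NIV in the presence of mediators".

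Steps 2 to 4 name neither baseline RS-NIV nor a baseline mediator score, and none of them says level or change.

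Elsewhere the article describes the primary outcome in two ways. The abstract says "The primary outcome of the trial is change in the hospital rate of NIV use among patients with COPD requiring ventilatory support", and both the primary analysis in Statistical analysis of aim 1 and the power section also use change from baseline. The section Primary outcome gives a level: "Hospital-level risk-standardized (RS) initial NIV proportion among patients hospitalized with a COPD exacerbation that were ventilated with NIV or IMV".

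The baseline values exist. Secondary outcomes says that all outcomes are measured over the 18 months before the trial. The Aim 2 Study design section schedules a baseline survey. Aim 1 already uses the baseline rate as a covariate: "A secondary analysis will compare the post-intervention levels, adjusting for baseline RS-NIV".

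**The concern.** Only the arm is randomised. Stratifying by baseline NIV proportion balances the arms, but it does not make hospitals with high and low autonomy scores comparable. The mediator-to-outcome path is an observational comparison across 20 hospitals.

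The article gives some reason to expect a link that predates the training. Its formative interviews in "a sample of hospitals with high use of NIV suggested that RT autonomy is critical to achieving timely initiation of NIV", and the Background lists RT autonomy and teamwork among the factors behind successful NIV use. If a hospital's earlier practice shapes both its 1-year survey score and its later RS-NIV, a model without a baseline term attributes part of that history to the mediator. Multiplied by any IPE effect on the score, this yields an indirect effect that need not reflect mediation, and the direct effect is wrong by the same amount in the opposite direction. Mediation by autonomy and/or team functionality is part of the central hypothesis and is the whole of Aim 2.

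**Working it through.** The plan gives no figure for this point, so there is none to reproduce. The check asks what each reading of the outcome yields when the mediator truly has no effect on NIV.

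**Inputs from the document.** 20 hospitals, 10 per arm; an arm difference of 15 points; and, from the Aim 2 power section, d = 0.4 with 10 RTs per hospital and ICC up to 0.20. The SD of a hospital mean score is then √(0.20 + 0.80/10) = 0.529, so the IPE shift in the mediator is a = 0.4/0.529 = 0.76 hospital-level SD.

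**Assumed inputs, not in the document.** SD of baseline RS-NIV between hospitals, s = 6, 9 or 12 points; within-arm correlation of baseline RS-NIV with the mediator, r = 0.3, 0.5 or 0.7; persistence of RS-NIV (slope of later on baseline), p = 0.85 or 0.5.

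**Formulas.** With no true mediator effect and no baseline covariate, the mediator coefficient per SD is p·r·s for the level and (p − 1)·r·s for change. The false indirect effect is a times that:

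| r, s | r·s | Level, p = 0.85 | Change, p = 0.85 | Level, p = 0.5 | Change, p = 0.5 |
|---|---|---|---|---|---|
| 0.3, 6 | 1.8 | +1.2 | −0.2 | +0.7 | −0.7 |
| 0.5, 9 | 4.5 | +2.9 | −0.5 | +1.7 | −1.7 |
| 0.7, 12 | 8.4 | +5.4 | −1.0 | +3.2 | −3.2 |

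For example, 0.76 × 0.85 × 4.5 = 2.9 points and 0.76 × (−0.15) × 4.5 = −0.5 points. Simulation of 4,000 trials per row (level, p = 0.85) gave 1.16, 2.97 and 5.39 points, which agrees. Against a total effect of 15 points, that column is 8% to 36%. The change bias is smaller than the level bias when p exceeds 0.5, and equal in size at 0.5.

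**False-positive rate of the mediator path** (nominal 5%, level, p = 0.85). With a residual SD of 8 it is 10%, 32% and 72% for the three rows. However, at s = 9 that residual SD implies an SD of change of √(8² + (0.15 × 9)²) = 8.1, while the stated 80% power for 15 points with 10 per arm implies about 11.3. At 11.3 the rates are about 8%, 21% and 56%. With p = 0.5 as well, they are about 7%, 13% and 34%.

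**With baseline RS-NIV in both equations.** The false indirect effect is about 0 and the error rate about 5%, for level or change. Subtracting baseline from the outcome only lowers the coefficient of baseline by 1; the arm and mediator coefficients do not alter.

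**Limit of the adjustment.** That zero assumes baseline RS-NIV is measured without error and is the only confounder. If its reliability is 0.6 (assumed), the adjusted level or change model still gives +0.5, +1.4 and +3.1 points at p = 0.85.

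**The case against.** A reader might infer that the plan will report earlier differences between hospitals as positive mediation. The document does not support that.

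- **The outcome may be change.** The abstract, the primary analysis and the power section all use change, and this is the more natural reading of a primary outcome. Baseline is then already subtracted and the bias changes sign. This objection stands. It makes the claim conditional but does not remove it, because Aim 2 never says change and the change model is not free of bias either.
- **A term that is not named may still be planned.** This is a condensed article, an analysis plan may exist, and the mediation diagram is not reproduced. Hospital factors are to be evaluated as potential confounders under Patient and hospital information. This stands in part. However, the section does set out its model sequence and places its one adjustment sentence with the mediator models.
- **The evidence for a prior correlation is thin.** The interviews were qualitative and came from high-NIV hospitals only. Trial hospitals are selected for low NIV use, which would tend to weaken any correlation. This stands: the range 0.3 to 0.7 is illustrative.
- **A false indirect effect also needs IPE to move the mediator.** This is correct for its average. The plan expects and powers for such a shift, and the mediator coefficients in steps 2 and 3 are biased without it.
- **Adjustment is not a full cure.** This stands. With a noisy baseline and high persistence, an unadjusted change model can even be less biased (−0.2 to −1.0 points) than the adjusted model (+0.5 to +3.1).

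**Conclusion.** The concern holds in conditional form. The Aim 2 section leaves open whether it models level or change and names no baseline term on a path that randomisation does not protect. If earlier NIV use and the mediator scores are correlated across hospitals, the indirect effect is biased upward under the level reading (about 1 to 5 points at persistence 0.85, about 0.7 to 3 at 0.5) and downward under the change reading, by less whenever persistence exceeds 0.5. These sizes rest on an assumed correlation, baseline SD and persistence, and on the plan's d = 0.4 being achieved. The highest false-positive rates require the level reading and the most extreme inputs together. If the correlation is zero, there is no bias from this source. The primary comparison of the arms in Aim 1 is not affected.

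**What to change.** In the Aim 2 Statistical analysis section:

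1. State whether the RS-NIV outcome is the post-intervention level or the change from baseline.
2. Include hospital baseline RS-NIV as a covariate in every model with RS-NIV as outcome, and in both the mediator and the outcome equation of the SEM. Level and change then give the same arm and mediator coefficients.
3. Add the hospital's baseline mediator score, at least as a sensitivity analysis. Showing the unadjusted change model beside it would reveal how far the result depends on a noisy baseline.
4. Report the indirect and direct effects as exploratory, and say that adjustment can reduce confounding of this path but cannot guarantee its removal, because baseline RS-NIV is imprecise in small hospitals and other confounders may exist.

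The cost is a few sentences and one or a few of 20 hospital-level degrees of freedom. Baseline RS-NIV and the baseline survey are already to be collected.
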